##### Food Frequency Analysis

To calculate usual intakes (ie, ∑ frequency weight × nutrient content), individual-level reported frequencies of consumption (ie, per day, week, month, or year) for each of the FFQ items were multiplied with standard portion sizes [35], then with nutrient calculation algorithms based on the standard portion sizes. Next, usual daily food and nutrient intakes by question were derived based on summing nutrient or food intake levels for the macro- and micronutrients, prorating their frequencies accordingly (eg, divisor of 365 for a given nutrient value if frequency of intake for the food is yearly) to provide daily nutrient or food intake values. Finally, total daily values for a given nutrient will be calculated by summing the appropriate cluster of FFQ variables that contain the nutrient of interest.

#### Descriptive Analysis

Descriptive analysis includes reporting of means (±SDs) or medians (with interquartile range) depending on continuous variable distributions. Subject characteristics between the I and C groups will be compared. The distributions of nutrient intakes will be examined and appropriately transformed if they deviate from normality.

#### Inferential Analysis

Inferential analysis includes Student *t* tests, analysis of variance (ANOVA), and Fisher exact tests to compare differences between groups and pre- and postinterventions. Analysis of the primary outcome measures involve conducting a series of repeated measures ANOVAs, comparing scores for each of the groups on the primary outcome measures (ie, food intake) at baseline and 8 weeks after receiving gene test results. The second set of analyses will involve using repeated measures ANOVAs to compare the 2 groups on measures of the different covariates. All analyses will be done on an intent-to-treat basis (last observation carried forward) using StataCorp’s STATA software [47].

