**Methods:**

This 4-month study used a mixed-methods design that included (1) a phase 1 randomized controlled trial that examined the effectiveness of a multifaceted, nutrition-based gene test (components assessed included major nutrients, food tolerances, food taste and preferences, and micronutrients) in changing health behaviors, followed by (2) a qualitative investigation that explored participants’ experiences. The study recruited 55 healthy males and females (aged 35-55 years) randomized as a 2:1 ratio where 36 received the intervention (gene test results plus integrated and personalized nutrition report) and 19 were assigned to the control group (gene test results report emailed). The primary outcomes of interest measures included changes in diet (nutrients, healthy eating index), changes in measures on General Self-efficacy and Health-Related Quality of Life scales, and anthropometrics (body mass index, waist-to-hip ratio) measured at baseline, post intervention (3 and 6 weeks), and the final visit (week 9 post intervention).

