### Objectives

The overall goal of this study was to investigate whether personalized dietary advice based on genotypic testing provided by a practitioner leads to greater dietary improvements and health outcomes compared with a nonpractitioner-assisted direct-to-consumer (DTC) self-driven approach. The main study objective was to compare a practitioner-facilitated personalized dietary approach that uses genotypic and phenotypic information with a DTC self-driven approach and their impact on changing participant’s knowledge, motivation, and behavior related to diet and eating and the quality of their diet. It was hypothesized that significantly higher levels of knowledge, motivation, and behavior would be reported, and there would be increased diet quality changes in the group that receives personal DNA diet information and customized dietary advice (practitioner-led) compared with the group that is provided personal DNA diet information (DTC self-driven approach) only. In addition to this primary objective, changes in self-efficacy were evaluated to determine whether it was a potential mediator/moderator of dietary changes, and changes in quality of life were assessed as a possible additional benefit to dietary changes. Focus group interview data were also collected to explore participants’ experiences with using personalized nutrition tools and resources.

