##### Covariates

Other relevant measures that can influence dietary intake and health behavior were assessed and controlled for. These included:

*Natural health product (NHP) usage:* NHP use (eg, vitamins, minerals, botanicals), which can influence nutrient intakes, is recorded at all study time points and included type, dose, and frequency of use. Participants were advised at baseline to keep any NHP use at the same dose and frequency throughout the study.*Physical and sedentary activities:* To measure activity level, physical activity index (PAI) [42] was used. The PAI included questions about the frequency, duration, and intensity of participation in certain activities in the previous 3 months. The data on physical activity were combined to obtain the PAI, which represents the average daily energy expended on leisure-time physical activity, expressed in kilocalories per kilogram body weight per day. To calculate this index, the energy expenditure (EE) for each activity was first estimated (see Multimedia Appendix 1 for details). The overall EE totals are used to categorize individuals as inactive (PAI <1.5 kcal/kg/day), moderately active (PAI 1.5 to <3 kcal/kg/day), and active (PAI ≥3 kcal/kg/day).*Sleep quality*: The Patient-Reported Outcomes Measurement Information System Sleep Disturbance scale-short form [43] is used to assess sleep quality. The instrument is an 8-item self-rated questionnaire, which assesses sleep quality over the previous 7 days. Individual items are scored on a scale from 1 to 5, and scores are summed to yield a total raw score between 8 and 40, with lower scores indicating better sleep or a lesser degree of sleep-related impairments.*Stress*: Because one’s ability to deal with stress can impact dietary intake, 2 validated questions from the Canadian Community Health Survey [44] are included as covariates.*Sociodemographics*: Standard determinants of health are measured that include sex/gender, age, relationship status, income, race/ethnicity, and perceived social support. The questions have been previously validated in studies such as the Canadian Community Health Survey.

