## Results

Four hundred and seventy-eight persons expressed interest in study participation in March 2017. Participants were invited sequentially from this list. This resulted in the study coordinator contacting a total of 180 of the 478 (37.6%) interested individuals who then completed the online eligibility-screening questionnaire. Given that most interested individuals were female, attempts were made to balance the sample by sex. Seventy-three of the 180 invited individuals (40.5%) were deemed eligible. Of those who were deemed to be eligible, 55 completed the baseline health questionnaire and food records (75%). The majority of participants are female, married, and have postsecondary education. To date, 3 participants were excluded (5%). This occurred before the first visit as they did not complete all required data collection forms or were later found to be eligible. No AEs have been reported.

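### The primary dietary analysis names no treatment-effect term, and its natural reading (group-by-time over two time points) is valid but less efficient than adjusting for the baseline already collected

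*Protocol article*

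**What the plan says.** The Inferential Analysis section of the protocol article fixes the method for the primary outcomes: "Analysis of the primary outcome measures involve conducting a series of repeated measures ANOVAs". It describes these as comparing scores for the groups "at baseline and 8 weeks after receiving gene test results", with food intake given as the primary outcome. The same section lists t tests, ANOVA and Fisher exact tests "to compare differences between groups and pre- and postinterventions". It does not say whether the group, time or group-by-time term answers the trial's question.

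The Objectives section states that question as a between-group one: whether practitioner-led advice "leads to greater dietary improvements and health outcomes compared with a nonpractitioner-assisted direct-to-consumer (DTC) self-driven approach".

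On covariates, two sections differ. The Covariates section, which lists sex/gender among the sociodemographics, says: "Other relevant measures that can influence dietary intake and health behavior were assessed and controlled for". The baseline value of the outcome is not in that list. The Inferential Analysis section mentions covariates only as things to be analysed themselves, "using repeated measures ANOVAs to compare the 2 groups on measures of the different covariates", and puts none of them into the outcome model.

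**The concern.** A two-group, two-time repeated-measures ANOVA produces three tests: group, time and group-by-time. Only the last is the randomized comparison of change, and the article does not name it. The choice of method is therefore fixed while the decisive contrast is left open, with pre/post tests available beside it.

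Two things are at stake. The first is precision: 55 participants split 36 to 19 is a small trial, and the test implied by the plan does not make the best use of a baseline record that every participant has already supplied. The second is interpretation. Both arms receive their gene results and the same follow-up emails (Description of Study Groups), so a change common to both arms is plausible. With unequal arms, separate within-arm tests can then differ in significance without any difference between the arms.

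**Working it through.** **What can be reproduced.** The article gives no power figure for the primary dietary outcome. Its one explicit sample-size result is a minimum of 16 per group for self-efficacy and quality of life, with no effect size, SD, correlation, alpha or power. At two-sided 5% and 80% power (normal approximation), 16 per group corresponds to (1.96 + 0.84) × √(2/16) ≈ 0.99 SD of whatever quantity was tested. That cannot be checked further and contradicts nothing below.

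**Inputs.**
- Arm sizes 36 and 19 (abstract, Methods).
- Two time points (Inferential Analysis).
- Assumed: outcome SD of 1 at both times; pre-post correlation r of 0.3, 0.5 or 0.7; effect of 0.8 SD, with 0.5 SD as a second case; two-sided 5%.

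**Formulas.**
- The group-by-time test with two time points is a t test on change, with variance 2(1 − r).
- ANCOVA on baseline has residual variance 1 − r².
- Ratio: (1 − r²) / [2(1 − r)] = (1 + r)/2, which is below 1 for every r below 1.
- Standard error factor for 36 v 19: √(1/36 + 1/19) = 0.2836.
- Noncentrality = effect / (SD × 0.2836). Power comes from the noncentral t distribution with 53 df for change and 52 df for ANCOVA.

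**Effect 0.8 SD.**

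| r | Variance ratio | SD, change | SD, ANCOVA | Noncentrality, change | Noncentrality, ANCOVA | Power, change | Power, ANCOVA |
|---|---|---|---|---|---|---|---|
| 0.3 | 0.65 | 1.183 | 0.954 | 2.38 | 2.96 | 64.8% | 82.7% |
| 0.5 | 0.75 | 1.000 | 0.866 | 2.82 | 3.26 | 79.1% | 89.2% |
| 0.7 | 0.85 | 0.775 | 0.714 | 3.64 | 3.95 | 94.7% | 97.2% |

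**Effect 0.5 SD.** Power is 31.0% v 44.2%, 41.0% v 51.5% and 60.8% v 67.8% at the same three correlations.

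At r = 0.3 the change-score test is weaker than a comparison of follow-up values that ignores baseline altogether (64.8% v 79.1%), because 2(1 − r) exceeds 1 whenever r is below 0.5.

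**Validity.** In a simulation of 3,000 trials per setting with no effect, the rejection rate was 5.3% to 5.8% for group-by-time and 5.1% to 6.1% for ANCOVA. Both are valid tests. The same simulation at 0.8 SD gave power within one percentage point of the table.

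**Within-arm tests.** Assume both arms change by 0.4 SD at r = 0.5 with no difference between them. The SD of change is 1, so the noncentrality is 0.4 × √36 = 2.40 in the arm of 36 and 0.4 × √19 = 1.74 in the arm of 19. The tests are significant with probability 64.6% and 37.9%. The pattern of significance in the intervention arm only then has probability 0.646 × (1 − 0.379) = 40%, although the arms do not differ.

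**The case against.** The strongest reply is that the plan already contains a valid randomized comparison that uses baseline. Group-by-time tests the difference in change, and the Objectives are worded in terms of greater improvement in one group, so it is the natural reading. The Study Design section calls the trial an exploratory pilot, and a condensed article may leave exact model terms to a fuller document. The size of the gain also depends on figures that the article does not give. All of this stands, and it limits the point to efficiency and clarity. It does not remove the point: the article itself commits to the method, and the better analysis needs no further data.

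Three stronger readings are tempting, and the documents do not support them.

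- A reader might infer that the group main effect, which averages in the pre-intervention record, is the planned treatment effect. The article never says so, and the Objectives point to group-by-time.
- A reader might infer that sex was overlooked, or that chance imbalance in sex undermines the analysis. The Covariates section lists sex/gender among the measures controlled for, and a stable additive sex effect cancels from a change score. The remark that "attempts were made to balance the sample by sex" concerns who was recruited, not how they were allocated.
- A reader might infer from the abstract's statement that the trial "examined the effectiveness of a multifaceted, nutrition-based gene test" that pre/post tests will be offered as proof that gene testing works. The wording is loose, since both arms receive results. But the abstract's Objective, the Objectives section and the Study Design section all state the comparison correctly, and nothing in the analysis section makes that use of the pre/post tests.

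**Conclusion.** The planned primary analysis is valid on its natural reading, but it is less efficient than it need be and does not name its treatment-effect term. ANCOVA has 65%, 75% and 85% of the change-score variance at r of 0.3, 0.5 and 0.7. For a 0.8 SD effect at 36:19 that is a gain of about 18, 10 and 2.5 percentage points of power. The results rest on an assumed effect size, assumed correlations and equal SDs at the two times. The direction holds for any r below 1 under equal SDs; the size does not, and at r of 0.7 or above the gain is modest. The risk from within-arm tests depends likewise on an assumed common change, but it is enough reason not to treat them as evidence of a difference between arms.

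**What to change.** In the Inferential Analysis section:

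1. Make the primary test for each primary dietary outcome the group coefficient from a linear model of the 8-week value on group and the baseline value of that outcome, reported as an adjusted mean difference with 95% CI.
2. State that within-arm pre/post tests are descriptive and are not evidence of a between-group effect.
3. Reconcile this section with the Covariates section. Entering sex in the same model is one simple way, since the article says that sex is controlled for.

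The cost is a few sentences of wording and a different model command, with no new data. The abstract's Conclusions say that the quantitative data have not yet been analysed, so the choice can still be recorded before any result could influence it.

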**Results:**

Of the 478 individuals who expressed interest, 180 were invited (37.7%, 180/478) and completed the eligibility screening questionnaire; 73 of the 180 invited individuals (40.5%) were deemed eligible. Of the 73 individuals who were deemed to be eligible, 58 completed the baseline health questionnaire and food records (79%). Of these 58 individuals, 3 were excluded either because they did not complete all required data collection forms or were later found to be ineligible. The final sample (n=55) was mostly female (75%), married (85%), and those who had completed postsecondary education (62%).

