### Study Participants and Setting

Participants included adults (aged 35-55 years) who were deemed eligible based on various criteria (Textbox 1). This age range was selected as people tend to typically notice changes in their health [24]. Sample size determination was based on estimated mean differences in diet quality scores used in a personalized nutrition intervention study [21], application of sample size for 2-sample comparison of means for repeated measures [25], and estimated rate of loss to follow-up of 10% (3/32). Using similar approaches and previous study results [26,27], we determined we would need a minimum of 16 participants per group to detect differences in self-efficacy and quality of life.

Study participation: inclusion and exclusion criteria.Inclusion criteriaAdults, aged 35-55 yearsAbility to understand, sign an informed consent, and to provide a buccal DNA swabWilling to improve healthMedically stable. Subjects with diet-related chronic disease can enroll provided that their condition was stabilized or well controlled for at least 6months at the time of the baseline visitExclusion criteriaCurrently on a therapeutic or restrictive diet (eg, Atkins)Diagnosis of 2 or more chronic diseases or unstable chronic disease as deemed by accepted clinical guidelinesClinical diagnosis of any mental health conditionAny of the following conditions: HIV; chronic obstructive pulmonary disease; severe/uncontrolled asthma; cystic fibrosis; bronchiectasis; interstitial lung disease; chronic renal failure; colon or small intestine problem; liver or kidney disease; uncorrected hypothyroidism or hyperthyroidism in the previous 12 months; alcohol or drug dependence during the previous 12 months; current or former malignancy for which the participant has undergone resection, radiation therapy, or chemotherapy within previous 5 yearsCurrently enrolled or plan to be enrolled in another research study during the course of the investigationPlanned or recent (within the last 12 months) bariatric surgeryCurrent use of weight-altering medication for the purpose of weight lossInvestigators and their immediate families, with immediate family defined as a spouse, parent, child, or sibling, whether biological or legally adoptedPregnant and/or breastfeedingCurrent smokerBody mass index ≥35Any other health risk or condition that may put the participant at risk, or influence the results of the study or the participant’s ability to participate in the study

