#### Recruiting/Screening: Online

Participants who entered the screening phase electronically signed an online informed consent form to grant permission to collect eligibility information and baseline health information (if deemed eligible). If the participant met the inclusion criteria, they were sent a 3-day food record to complete within 7 days (±3 days) of their first site visit. In addition, they were sent the link to complete an online baseline assessment questionnaire that collected information about sociodemographics, their health (eg, presence of any health conditions, medications, supplements used), health-related quality of life (Short-Form 8, SF8), self-efficacy (General Self-Efficacy, GSE), physical and sedentary activities, food intakes (food frequency, food selection), and sleep quality.

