#### Nutrition Outcomes

Three-day food records measured pre- and postnutrient intakes including daily eating patterns. Changes in caloric, macronutrient, micronutrient, and food groups will be measured and compared with national standards (eg, *Eating Well with Canada’s Food Guide*, *Dietary Reference Intakes*). Changes in overall diet quality will be assessed using the Canadian version of the Healthy Eating Index [34]. Protocols for food record data collection will be derived from Health Canada nutrition survey procedures [35].

In addition to nutrient intake information collected from the food records, a food frequency questionnaire (FFQ) is included to assess for usual intakes and to validate the food record information. The food frequency measurement tools were derived from Health Canada nutrition survey measures [35].

Nutrition measures also included food selection questions about types of food selected, dietary restraint, food insecurity, motivation to change diet, and eating behavior changes. These were based on validated measures such as the Three Factor Eating Questionnaire [36], Health Canada, Statistics Canada (eg, the Canadian Community Health Survey), and BC Ministry of Health surveys [35], as well as review of the research literature about measurements of motivation and dietary change and eating behavior changes. Some of these questions were developed by the research team and pilot-tested for comprehension and face validity.

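### For food records and anthropometrics, the intent-to-treat rule (last observation carried forward) carries the baseline forward and gives anyone without a second measurement a change of exactly zero

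*Protocol article*

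**What the plan says.** The protocol article's Inferential Analysis section sets one missing-data rule for every analysis: "All analyses will be done on an intent-to-treat basis (last observation carried forward". The parenthesis presents the imputation rule as the content of intent-to-treat. The same section compares the groups by repeated measures ANOVA on the "primary outcome measures (ie, food intake) at baseline and 8 weeks after receiving gene test results".

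The food-record times are these:
- **Before the intervention.** Eligible participants "they were sent a 3-day food record to complete within 7 days (±3 days) of their first site visit" (Recruiting/Screening: Online; Table 1, V1).
- **After the intervention.** One record is sent after the week 6 check-in and brought to the final visit (Three- and Six-Week Online Check-Ins; Table 1 ticks it at V5). Nutrition Outcomes describes the same pair: "Three-day food records measured pre- and postnutrient intakes including daily eating patterns".
- **Later.** Table 1 has one more record, for the control group only, 4 weeks after the final visit. By then the controls have received the intervention.

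Table 1 places anthropometrics at V2 and V6 only. The one loss figure given is in Study Participants and Setting: "estimated rate of loss to follow-up of 10% (3/32"). The abstract gives 36 intervention and 19 control participants and reports very high retention, but not by arm.

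**The concern.** Intent-to-treat means analysing people in the group to which they were randomized. Last observation carried forward is a separate decision about what value to give someone who was not measured. With one measurement before and one after, only the baseline is available to carry. The rule therefore assumes, with certainty, that a participant without the second record did not change at all.

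That is a strong assumption here. Participants had to be willing to improve their health, and both arms receive gene results and three emails with tips and reminders, so some change is plausible in both. Only one arm is counselled by a dietitian, so unequal loss is possible too. The estimated effect may then be diluted, or shifted in a direction set by which arm loses more people. The ANOVA would treat the imputed zeros as real data. The article says the quantitative data have not been analysed, so the rule can still be changed without knowledge of the results.

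**Working it through.** **Planned loss.** 3/32 = 9.4%, and 10% of 32 = 3.2, so the article's 10% is a rounded figure. Applied to the 55 randomized, 0.10 × 55 = 5.5, or about 5 to 6 participants with imputed values.

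**Algebra.** Let m be an arm's mean true change and d its share without a second record, with missingness unrelated to outcome. Each missing person has post = baseline, so change = 0. The arm mean becomes m(1 − d), and the estimated difference is

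m_I(1 − d_I) − m_C(1 − d_C).

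**Assumed inputs.** The article gives no effect size, SD, alpha or loss by arm. I take a baseline SD of 1 and a pre-post correlation of 0.5, so the SD of change is √(2 × (1 − 0.5)) = 1. Group sizes are 36 and 19. Rejection rates come from simulated two-sided 5% t tests on change scores, which are equivalent to the group-by-time test with two times.

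| True change, I / C | Loss, I / C | Difference under the rule | True difference | Rejection under the rule | Rejection, observed data |
|---|---|---|---|---|---|
| 0.6 / 0 | 10% / 10% | 0.6 × 0.90 = 0.54 | 0.60 | about 0.49 (power) | about 0.50 (power) |
| 0.6 / 0.6 | 10% / 10% | 0.54 − 0.54 = 0 | 0 | about 5% | about 5% |
| 0.6 / 0.6 | 5% / 10% | 0.57 − 0.54 = +0.03 | 0 | about 5% | about 5% |
| 0.6 / 0.6 | 5% / 25% | 0.57 − 0.45 = +0.12 | 0 | about 6.5% | about 5% |
| 0.6 / 0.6 | 25% / 5% | 0.45 − 0.57 = −0.12 | 0 | about 8% | about 5% |
| 0.3 / 0.3 | 5% / 25% | 0.285 − 0.225 = +0.06 | 0 | about 5% | about 5% |

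A harsher scenario has both arms improving by 1 SD and whole participants lost from one arm only:
- 7 of 36 lost from intervention, none from control: 29/36 − 1 = −0.19.
- None lost from intervention, 4 of 19 from control: 1 − 15/19 = +0.21.
- Type I error is about 10% in both.

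**When missingness is related to outcome.** Suppose the 10% without a second record have in fact gone back to their previous diet, and the others in the intervention arm improved by 0.60 against none in control. The true difference over everyone randomized is then 0.9 × 0.60 = 0.54. Baseline carried forward returns 0.54; observed data return 0.60. The ranking of the two methods therefore depends on an assumption that the trial's data cannot settle.

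**The case against.** **Size at the planned loss.** With 10% in both arms the rule is mildly conservative: 10% attenuation, about a point of power, no excess false positives. The study is described as an exploratory pilot, and retention is reported as very high. This stands, and it is why the point is not critical.

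**The larger figures rest on undocumented inputs.** Nothing in the article supports 5% versus 25% loss or a 0.6 SD improvement in both arms. The case with 25% lost from intervention loses 0.25 × 36 + 0.05 × 19 ≈ 10 of 55, or 18%, nearly double the plan. This stands too; the figures show a range, not a forecast.

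**Zero change could be right.** If people who stop return to their old diet, the rule is correct and an observed-data analysis overstates the effect. The defect is therefore an untested assumption built into the primary analysis, not a demonstrated bias.

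**Stronger readings to avoid.**
- A reader might infer that every dropout on every outcome is set to zero change. The check-in section says the baseline measures were repeated at 3 and 6 weeks, and these include SF-8, GSE and the food frequency questionnaire. A post-intervention value may exist to carry for those, although Table 1 ticks them only at V5. Someone who returns the second food record and then misses the final visit also keeps an observed food-record value.
- Conversely, the abstract lists its outcomes together with 3- and 6-week times, which might suggest interim diet and anthropometric data. Table 1 and the visit descriptions show no food record or body measurement then.
- A reader might infer that the intent-to-treat set is uncertain. The abstract says "58 completed the baseline health questionnaire and food records (79"%), less 3 exclusions; the Results section says "55 completed the baseline health questionnaire and food records (75"%), then mentions 3 exclusions, which could read as 52. But Results places those exclusions before the first visit, randomization falls between visits 2 and 3, and 36 + 19 = 55. This is a separate clerical slip in the recruitment flow.

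**Conclusion.** The point holds for food records and anthropometrics: there the stated rule is baseline carried forward, and a missing second measurement becomes a certain change of zero. Under missingness unrelated to outcome, the cost at the planned 10% loss in both arms is a 10% shrinkage of the effect (0.60 to 0.54 SD), with type I error intact. With unequal loss and improvement in both arms, the bias has either sign. It runs from about 0.03 SD with no visible effect on type I error to about 0.12 SD with 6.5 to 8% type I error, and more only in harsher scenarios. The effect sizes, SD and loss by arm are assumptions. The article supports neither a claim that the trial's result will be biased nor a claim that the defect affects all outcomes. Severity: should fix, before the data are analysed.

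**What to change.** - **Define the set.** State intent-to-treat as analysing all 55 randomized participants (36 and 19) in their allocated group, and remove the equation with last observation carried forward.
- **Replace the primary method.** Use either a likelihood-based mixed model that includes every participant's available food-record data, or multiple imputation followed by a baseline-adjusted analysis. Use baseline and check-in questionnaire data, including the food frequency questionnaire, as auxiliary variables under missing-at-random. Baseline-adjusted regression alone cannot cover all 55, because someone without a second record has no outcome. With only two food-record times, a mixed model gains little over observed cases; any real gain comes from the auxiliary data.
- **Keep the present rule as a labelled sensitivity analysis**, for the case where people who stop return to their previous diet. Report missing second records by arm.
- **Treat anthropometrics in the same way.** For outcomes measured at the check-ins, use all observed times.
- **Separately, correct the recruitment counts** in the Results section to agree with the abstract.

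Cost: changed analysis wording and somewhat more analysis work with standard Stata commands; no new data. The price is reliance on missing-at-random, which the sensitivity analysis probes.
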